## 8) Statistical analysis

### 8.1 Sample estimation

We assume a first pass without PVWP rate of 95% and 90% for the MCSL and OA-IP methods, respectively. The non-inferiority bound is pre-set as a primary outcome difference between groups of -8%. We estimate that 85 patients in each group would provide 90% of the power at the 0.025 level to compare the MCSL approach with the OA-IP approach. Considering the 10% shedding rate, ultimately, we intend to enroll 95 patients in each group.

### 8.2 Data management and Statistical Analysis

The data of case report form was recorded by two persons in two copies. The data was entered in Excel 2010 and an analysis database was established. The database was locked after verification. SPSS 25.0 software and Stata 13.0 software were used for statistical analysis of data. Continuous quantitative data were expressed as mean (SD) or median (interquartile

range, IQR). The normality of the data distribution is assessed by the Kolmogorov-Smirnov test. The Levene test is used to test the homogeneity of the variance. For continuous variables that satisfy the normal distribution and independent measurements, an independent sample t test or a corrected t test is used for analysis based on the homogeneity of variance. Continuous variables with non-normal distribution were analyzed by Mann-Whitney U test. Qualitative variable data were expressed as numbers and percentages. Categorical data were analyzed using the  $\chi^2$  test or the exact Fisher test based on theoretical frequency and sample size. Multivariate analysis was performed using logistic regression and linear regression to control for possible confounding factors. P value < 0.05 is considered statistically significant.

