**Sponsor: Chongqing University Cancer Hospital**

## **1. Background of the research**

As a routine clinical operation, central venipuncture has played a great role in clinical treatment. It includes emergency rapid blood transfusion, infusion, invasive hemodynamic monitoring, infusion of vasoactive drugs, chemotherapy drugs, parenteral nutrition drugs and hemodialysis. The internal jugular vein (IJV) is one of the most common options for establishing central venous access. With the rapid development of economy in our country and the change of modern lifestyle and dietary structure, the adult obesity in our country is as high as 160 million, the obesity rate about 11.9%. The traditional anatomic marker location IJV puncture catheterization often leads to the difficulty of puncture catheterization in obese patients, and is prone to various mechanical complications, such as misplaced artery puncture, hematoma, pneumothorax, etc. Ultrasound-guided internal jugular vein catheterization can significantly reduce the risk of puncture-related complications and improve the success rate of one-time puncture.

At present, clinical studies mainly focus on the comparison of short-axis method, long-axis method, oblique axis method and the improved methods of the above methods, in order to find the safest and most efficient ultrasound-guided IJV puncture catheter method. A large number of studies have shown that the oblique axis method and the improved combined method show advantages. By comparing oblique axis method and modified combined short and long axis method, this study intends to study the differences in ultrasonic anatomy of obese patients under oblique axis and short-axis method, and compare the differences in puncture time, puncture success rate and puncture complications between the combined method and the oblique axis method, so as to find the ultrasound-guided IJV puncture method that is most suitable for obese patients, and promote the technology to improve the regional medical technology level. It is of great clinical significance.

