### **6.2.2 Puncture and image acquisition protocol**

All right internal jugular vein puncture catheterization procedures will be performed by the same senior attending physician who is proficient in both methods. A one-man technique will be used (the same operator operated the ultrasound probe and puncture needle) using the 12L5-A high frequency probe of the Mindray M9T notebook color ultrasound diagnostic system with a probe length of 4.7cm (set frequency 7.5-10 MHz and depth of 5cm). After the patient be anesthetized, the pillow will be removed and the patient lay flat with the head tilted 30 degree to the left and the head low and the foot high at 15 degree. Before preparing for skin disinfection, preoperative ultrasound examination will be performed to identify IJV and CCA in the images (generally IJV is shallower than CCA, the vessel wall is thin, the diameter is thick, the lumen is oval, the size can change with breathing, and the probe can be pressed flat; CCA position is deep, the blood vessel wall is thick, the diameter is thin, the lumen is round, and the probe pressure can not squish it. Color Doppler ultrasound imaging technology will be used, and the probe will be oriented towards the proximal end. It could be seen that the red blood flow signal area is CCA, while the blue blood flow signal area is IJV), patency of the internal jugular vein. The adjacent relationship between IJV and CCA in the short axis plane and oblique axis plane of all patients will be observed at the thyroid cartilage level, and ultrasound images will be collected and saved.

After the images be saved, the modified combined short and long axis method and oblique axis method will be performed according to the group conditions. First, routine disinfection will be performed, sterile tissue will be laid, the ultrasonic probe will be put into the sterile protective cover, and 10 ml of sterile ultrasonic coupling agent will be injected into the protective cover, and the probe cover will be fixed. In the modified combined short and

long axis method, ultrasonic probe will be fixed the radiopaque barium line at the center line of the probe in advance. The two groups of operation methods are as follows:

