## 7.2 Secondary outcome indicator

① IJV insertion time, define: from the beginning of needle insertion to ultrasound confirmation that the guide wire be in the IJV and in the correct position. ② Total puncture time, defined: from the beginning of needle insertion to catheter fixation, and the position is correct. ③ IJV transverse diameter, CCA and IJV overlapping rate ([IJV and CCA overlapping distance /CCA transverse diameter] x 100%), safe puncture distance =IJV transverse diameter - IJV and CCA overlapping distance, CCA and IJV relative position relationship. ④ The number of punctures (each time the puncture needle recedes and adjusts the direction is regarded as a puncture). ⑤ The total success rate of puncture (puncture times >3 or complications are regarded as failure, and other central veins are replaced to complete puncture catheterization). ⑥ Puncture complications, such as hematoma, mispuncture artery, external jugular vein injury, thyroid injury, nerve injury, pneumothorax and hemothorax, etc. (combined with the puncture operator, puncture operation video and imaging data to determine the judgment of pneumothorax and hemothorax by experienced imaging doctors according to the chest film to judge).

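### Secondary outcome 3 is imaged in both planes in every patient, but section 8.2 names no paired method for comparing the planes

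*Protocol*

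**What the plan says.** - **Intent.** Protocol section 1 (Background) says that "this study intends to study the differences in ultrasonic anatomy of obese patients under oblique axis and short-axis method".
- **Data collection.** Section 6.2.2: "The adjacent relationship between IJV and CCA in the short axis plane and oblique axis plane of all patients will be observed", with the images saved. Only then does the randomised part begin: "After the images be saved, the modified combined short and long axis method and oblique axis method will be performed according to the group conditions".
- **Outcome.** Item 3 of section 7.2 begins "IJV transverse diameter, CCA and IJV overlapping rate" and goes on to safe puncture distance and the relative position of the two vessels. It does not say which contrast is to be tested.
- **Tests.** Section 8.2 names three kinds. For normal data: "For continuous variables that satisfy the normal distribution and independent measurements, an independent sample t test or a corrected t test is used". For the rest: "Continuous variables with non-normal distribution were analyzed by Mann-Whitney U test", and for categorical data a chi-square "test or the exact Fisher test based on theoretical frequency and sample size". It adds logistic and linear regression for confounding. It names no paired t test, signed-rank test, test of marginal homogeneity or mixed model.

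**The concern.** Each patient supplies two measurements of the same vessels, one per plane, taken before the allocated technique is carried out. A comparison of planes is therefore a comparison of paired values, whatever the randomised group. None of the tests named in section 8.2 is built for such data.

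The three test sentences fail in different ways. The t-test sentence applies only to independent measurements, so normally distributed paired data are left with no test. The Mann-Whitney and chi-square/Fisher sentences are triggered by data type alone. An analyst following them would treat the two planes as separate samples of patients.

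At stake are the intervals and P values for a comparison the protocol says it intends to make. There is also a risk that the analyst falls back on a group M versus group O comparison, which answers a different question.

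**Working it through.** **The plan's own figure.** The only sample-size calculation is for the primary outcome (section 8.1): rates of 95% and 90%, margin −8 points, one-sided 0.025, 90% power. With unpooled variance, n = (1.960 + 1.282)² × (0.95×0.05 + 0.90×0.10) / (0.05 + 0.08)² = 10.507 × 0.1375 / 0.0169 = 85.5, so 86 per group against 85 stated. Power at 85 is 89.8%, and 85/0.90 = 94.4, rounded up to 95. The figure reproduces to within one patient and does not bear on this point. No design figure is given for the anatomy comparison.

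**Inputs.**
- n = 190 patients, 95 per group (sections 3.1 and 3.4).
- Two-sided 0.05 (section 8.2 gives P < 0.05; two-sided is my reading).
- Within-patient correlation r between planes: not in the documents, so a range of 0.3 to 0.7 is assumed.
- Equal standard deviation s in both planes: also assumed.

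**Formulas for the variance of the mean plane difference.**
- Paired, 190 patients: 2s²(1 − r)/190.
- Treated as 190 versus 190 independent values: 2s²/190. Ratio to paired: 1/(1 − r).
- One plane taken from each group, 95 versus 95: 2s²/95. Ratio to paired: 2/(1 − r).
- True size of the nominal 0.05 unpaired test on 190 versus 190: 2[1 − Φ(1.960/√(1 − r))].
- Its power where the paired test has 80%: Φ(1.960 + 0.842 − 1.960/√(1 − r)).

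| Assumed r | Variance ratio, 190 v 190 | SE ratio | True size | Power (paired = 80%) | Equivalent number of pairs, of 190 | Variance ratio, 95 v 95 |
|---|---|---|---|---|---|---|
| 0.3 | 1.4 | 1.20 | 0.019 | 68% | 133 | 2.9 |
| 0.5 | 2.0 | 1.41 | 0.0056 | 51% | 95 | 4.0 |
| 0.7 | 3.3 | 1.83 | 0.0004 | 22% | 57 | 6.7 |

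A simulation (190 pairs, 4,000 runs per value of r) gave unpaired sizes of 0.020, 0.006 and 0.0008, against 0.050, 0.046 and 0.054 for the paired test. The variance ratios do not depend on n, so dropout does not change them.

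**Unequal standard deviations.** If one plane's SD is k times the other's, the 190 versus 190 ratio is (1 + k²)/(1 + k² − 2rk), which for positive r never exceeds 1/(1 − r). For example, k = 1.5 and r = 0.5 give 3.25/1.75 = 1.86 instead of 2.0. The tabulated variance ratios are therefore upper bounds at each r.

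**The between-arm alternatives.** Comparing the same plane in group M and group O compares values recorded before the allocated technique, that is, randomised baselines, and says nothing about planes. Comparing the short-axis plane in one arm with the oblique plane in the other is unbiased under randomisation, but it discards half the images and has the variances in the last column.

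**The case against.** The strongest reply is that section 8.2 never assigns an unpaired test to the plane contrast. Section 7.2 leaves the contrast open, the test list is the usual generic one for a two-arm trial, and the t-test sentence excludes dependent measurements by its own condition. On this view the protocol is silent rather than wrong, and the statistical analysis plan, which was not available, may name the method.

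For normally distributed data that reply stands: the sentence leaves a gap and does not prescribe a wrong test. It does not cover the other two sentences, which assign tests by data type with no independence condition. They are statements of the protocol itself, so the point goes beyond detail left to a later document.

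The reply is also right on importance. The plane comparison appears in the Background and not in the formal objective (section 2), and it concerns one of six secondary items.

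A reader might also infer stronger claims that the documents do not support:
- *Most of the information would be wasted.* For 190 versus 190 the share lost equals r under equal SDs: 30% at 0.3, half at 0.5, and more than half only above 0.5. The documents give no r. A loss above half at every positive r arises only with one plane per arm, which the protocol does not state.
- *Spurious findings would result.* With positive correlation the unpaired test is conservative.
- *Standard errors will be wrong.* That depends on an analysis the protocol does not commit to.

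**Conclusion.** The point holds in a limited form. The plane comparison for secondary outcome 3 is paired by design, and section 8.2 offers it either no test (normal data) or an unsuitable one (non-normal and categorical data).

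If the planes were analysed as independent samples, intervals would be too wide, P values too large and real differences more easily missed. The size rests on the assumed correlation and on equal SDs, and it is worked out for means only. The rank and categorical tests were not quantified. The conservative direction requires a positive correlation, which is to be expected for two views of the same vessels but is not stated in the documents.

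The primary non-inferiority analysis and the sample size are untouched. The correction is worth making before the data are analysed, but it does not threaten the trial's main conclusion.

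**What to change.** Add to section 8.2 that secondary outcome 3 is compared between the short-axis and oblique planes within patients, over all imaged patients:
- For IJV diameter, overlap rate and safe puncture distance, use a paired t test or Wilcoxon signed-rank test, with a confidence interval for the paired difference.
- For relative position, use McNemar's test if it has two categories, or Stuart-Maxwell if it has more.

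State that the independent t test, Mann-Whitney and chi-square/Fisher tests are for between-group outcomes, and name the plane contrast in item 3 of section 7.2. If a statistical analysis plan exists, carry the same wording there.

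The cost is a few lines of text. Both planes are already imaged and saved in every patient, so no new data, visits or patients are needed.

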## **3. Research Scheme**

## **1) Research design**

This is a single-center, randomized, controlled, non-inferiority, evaluator blind clinical study. The modified combined short and long axis method will be selected as the experimental group and the inclined axis method as the control group, and 190 subjects will be planned to be included in the study according to 1:1 balanced allocation.

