## **7) Outcome indicators**

### **7.1 primary outcome indicator**

① Successful first needle pass without posterior vessel wall puncture (PVWP). Insertion of the puncture needle into the IJV with no blood aspirated during aspiration, but visible blood return upon withdrawing the needle, which can be regarded as PVWP.

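### The stated test for the primary outcome is a chi-square or Fisher test of equality at P<0.05, which cannot test the -8-point non-inferiority margin on which the trial is sized

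*Protocol*

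**What the plan says.** Section 3, item 1 (Research design) sets the framework: "This is a single-center, randomized, controlled, non-inferiority, evaluator blind clinical study". Section 7.1 makes the primary outcome binary: success on the first needle pass without posterior vessel wall puncture.

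Section 8.1 sizes the trial on that outcome. The expected rates are: "We assume a first pass without PVWP rate of 95% and 90% for the MCSL and OA-IP methods, respectively". The margin, in percent, is: "The non-inferiority bound is pre-set as a primary outcome difference between groups of -8". The size follows: "85 patients in each group would provide 90% of the power at the 0.025 level", and then "Considering the 10% shedding rate, ultimately, we intend to enroll 95 patients in each group".

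Section 8.2 assigns tests by type of data. Categorical data go to the chi-square "test or the exact Fisher test based on theoretical frequency and sample size". Logistic and linear regression are added to adjust for confounders. One decision rule closes the section: "P value < 0.05 is considered statistically significant". The section does not mention the primary outcome, a risk difference, a confidence interval, the margin, the 0.025 level or a criterion for non-inferiority.

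**The concern.** A non-inferiority claim needs evidence that the true difference M minus O lies above -8 points. Chi-square and Fisher tests ask a different question, namely whether the difference is zero. A non-significant result does not show non-inferiority, because it may only reflect few patients. A significant result against M does not show that M is worse by more than 8 points. Only a significant result in favour of M would settle the matter, and that is a superiority finding for which the trial was not sized.

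Followed as written, section 8.2 gives no route to the primary claim except superiority. It also leaves room for the common misreading that P>0.05 means not inferior.

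**Working it through.** **Inputs.** From section 8.1: success rates 0.95 (M) and 0.90 (O), margin 0.08, level 0.025, power 0.90, dropout 10%. From section 8.2: chi-square or Fisher, P<0.05, taken as two-sided.

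**1. Reproduce the plan's sample size.** Unpooled normal approximation, one-sided 0.025:

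n = [0.95×0.05 + 0.90×0.10] × (1.960 + 1.282)² / (0.05 + 0.08)² = 0.1375 × 10.507 / 0.0169 = 85.49 per arm

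This rounds up to 86, against 85 stated. Power at 85 is Φ(0.13/√(0.1375/85) − 1.960) = Φ(1.272) = 89.8%. With dropout, 85/0.90 = 94.4, so 95. The plan's figures are therefore reproduced as a one-sided 0.025 non-inferiority calculation. Other levels do not fit: one-sided 0.05 gives 70 per arm and one-sided 0.0125 gives 101.

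**2. Power of the stated test by formula.** For a two-sided 0.05 test of equality at the same rates, with mean rate 0.925:

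- Power at 85 per arm: Φ[(0.05×√85 − 1.960×√(2×0.925×0.075)) / √0.1375] = Φ[(0.461 − 0.730)/0.371] = 23%. At 95 per arm it is 26%.
- Size for 90% power: (1.960×√0.13875 + 1.282×√0.1375)² / 0.05² gives 582 per arm (621 with continuity correction).

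**3. Exact enumeration.** All pairs of binomial counts were weighted by their probabilities:

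| Per arm | True rates M / O | Quantity | Chi-square | Fisher |
|---|---|---|---|---|
| 85 | 95% / 90% | P<0.05 | 22.5% | 15.7% |
| 95 | 95% / 90% | P<0.05 | 25.5% | 17.8% |
| 85 | 82% / 90% | not significant | 67.7% | 74.5% |
| 95 | 82% / 90% | not significant | 64.3% | 71.3% |

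The last two rows place M exactly at the margin, where a valid non-inferiority test should succeed about 2.5% of the time.

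**4. A rule that uses the margin.** The lower limit of the two-sided 95% confidence interval is compared with -8%:

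| Interval | Power, 85 per arm | Power, 95 per arm | False non-inferiority at 82% / 90%, 85 per arm |
|---|---|---|---|
| Newcombe | 88.3% | 90.6% | 2.4% |
| Wald | 91.3% | 93.7% | 2.8% |

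At the planned rates with 85 per arm, 69% of trials would show non-inferiority by the Wald limit while the chi-square test is non-significant. In those trials the stated analysis would miss the trial's own conclusion.

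**5. One possible result.** Take 77/85 on M and 80/85 on O. The difference is 0.9059 − 0.9412 = −3.5 points, with SE = √(0.9059×0.0941/85 + 0.9412×0.0588/85) = 0.0407. The Wald 95% interval is −11.5% to +4.4%, so -8% is not excluded. Fisher gives P=0.57. Section 8.2 would report no significant difference, yet non-inferiority is not shown.

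**The case against.** The strongest reply is that a statistical analysis plan may exist, and that the interval method and the wording of the decision rule are often left to it. Section 8.1 does fix the margin, the level and the power, and a reader could infer the right analysis from them. Section 8.2 is a generic paragraph by data type that never names the primary outcome. This would hold if the protocol were silent. It is not: it names a test and a threshold for all categorical data and exempts nothing. A separate plan with the correct test would contradict section 8.2, which would still need correcting.

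Some narrower points do stand:

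- Chi-square and Fisher are not strictly the only methods named, since logistic regression is mentioned. It is a general adjustment, is not tied to the primary outcome, works on the odds-ratio scale and does not refer to the margin.
- The 68% to 75% error is conditional. The protocol nowhere says that P>0.05 will be read as non-inferiority, but it offers no other rule.
- A significant result for M would imply non-inferiority. It would be a safe claim (about 0.03% of trials when M is 8 points worse, by chi-square at 85 per arm), but it is reached in less than a quarter of trials under the planned rates.
- A two-sided 0.05 test has 0.025 in each tail, so the two levels can be reconciled. The null hypotheses cannot.
- The aim in section 2 of finding the most suitable method is not a formal superiority hypothesis, so a superiority step is optional.

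**Conclusion.** The concern holds and must be fixed, because the primary conclusion depends on it. Sections 3 and 8.1 define a non-inferiority trial, and the test stated in section 8.2 has a zero-difference null and ignores the margin. Under the planned rates with 85 per arm it has 22% power (chi-square) or 16% (Fisher), where the protocol claims 90%. Used the wrong way round, it would pass a method at the margin about 68% to 75% of the time. These figures assume the rates in section 8.1, independent binomial counts, a two-sided P value and, for the error rate, that non-significance is taken as non-inferiority. The mismatch itself does not depend on any of these assumptions.

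**What to change.** Add a primary-analysis paragraph to section 8.2, for example:

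*The primary analysis estimates the risk difference (group M minus group O) in first-pass success without posterior wall puncture, with a two-sided 95% Newcombe confidence interval. Non-inferiority is concluded if the lower limit is above -8%. If non-inferiority is concluded, superiority is concluded if the same lower limit is above 0.*

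The last sentence is optional. Taking the two steps in that order on one interval costs no alpha. Miettinen-Nurminen limits are an acceptable alternative, but one method should be named in advance. Section 8.1 should say that 0.025 is one-sided, and the chi-square and Fisher tests at P<0.05 should be confined to the secondary outcomes.

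The cost is a few sentences, with no new data and no change to the 95 per arm. With Newcombe limits the power is just under the target at 85 evaluable per arm (88%) and meets it if all 95 are analysed (91%). The protocol should report that range or accept the small shortfall openly.

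### The adjusted analysis in Protocol 8.2 is a logistic model judged at P < 0.05, which as written does not address the absolute -8-point margin; ask for a standardised risk difference

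*Protocol*

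**What the plan says.** The trial is a non-inferiority comparison, and its primary outcome is binary: a successful first needle pass without posterior vessel wall puncture (Protocol, sections 1) Research design and 7.1).

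Section 8.1 sets the margin on the absolute scale: "The non-inferiority bound is pre-set as a primary outcome difference between groups of -8" per cent. The planning rates are also there: "We assume a first pass without PVWP rate of 95% and 90% for the MCSL and OA-IP methods, respectively". So is the sample size: "We estimate that 85 patients in each group would provide 90% of the power at the 0.025 level", then "Considering the 10% shedding rate, ultimately, we intend to enroll 95 patients in each group".

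Section 8.2 gives the analysis. Categorical data are compared by a chi-squared test or the "exact Fisher test based on theoretical frequency and sample size". Adjustment gets one sentence: "Multivariate analysis was performed using logistic regression and linear regression to control for possible confounding factors". The section closes with a general significance rule of P < 0.05. It names no effect measure for the logistic model, no covariates, no confidence interval and no link between this model and the margin.

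**The concern.** The natural reading is that logistic regression serves the binary outcomes and linear regression the continuous ones. Logistic regression is then the only adjusted method for the primary outcome, and the only stated way to judge it is whether P falls below 0.05.

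That tests an odds ratio against 1, which asks whether the two methods differ. The trial asks whether the experimental method is worse by 8 points or more. An adjusted result reported in the usual form would sit beside the primary result without confirming or challenging it. A reader could also take a non-significant adjusted odds ratio as support for non-inferiority, which it is not.

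**Working it through.** **Inputs.** All are from section 8.1: success 95% (experimental) and 90% (control), margin -8 points, level 0.025 (read as one-sided), power 90%, 85 evaluable and 95 enrolled per group. The P < 0.05 rule is from section 8.2.

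**1. The plan's own figure, on the risk-difference scale.**
n per group = (1.960 + 1.282)² × (0.95 × 0.05 + 0.90 × 0.10) / (0.95 - 0.90 + 0.08)² = 10.507 × 0.1375 / 0.0169 = 85.5.
The stated 85 gives 89.8% power, and 85 / 0.9 = 94.4, rounded up to 95. The figure reproduces, which confirms that the trial was planned on the absolute difference.

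**2. The margin as an odds ratio.** For control success c, the equivalent is odds(c - 0.08) / odds(c).

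| Control success | Calculation | Odds ratio at -8 points |
|---|---|---|
| 85% | (0.77/0.23) / (0.85/0.15) | 0.59 |
| 90% | (0.82/0.18) / (0.90/0.10) | 0.51 |
| 95% | (0.87/0.13) / (0.95/0.05) | 0.35 |

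The equivalent moves with a control rate that is unknown until the data are in. None of these values is 1, the value that a P < 0.05 rule tests.

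**3. Two illustrative results with 85 per arm** (treatment-only model, Wald intervals; the counts are chosen for illustration).

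| Successes, experimental vs control | Odds ratio (95% CI) | P | Risk difference (95% CI), points | Against -8 |
|---|---|---|---|---|
| 81 vs 76 | 2.40 (0.71 to 8.11) | 0.16 | +5.9 (-2.1 to +13.8) | met |
| 75 vs 77 | 0.78 (0.29 to 2.08) | 0.62 | -2.4 (-11.6 to +6.9) | not met |

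For the second row:
- Odds ratio = (75/10) / (77/8) = 0.78. The standard error of its log is √(1/75 + 1/10 + 1/77 + 1/8) = 0.501.
- Risk difference = -2/85 = -2.4 points, with standard error √(0.882 × 0.118/85 + 0.906 × 0.094/85) = 4.7 points.

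Both odds ratios are non-significant, and the non-inferiority conclusions are opposite.

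**4. The same model can answer the question.** In the first row, predicting each arm's success probability from the fitted logistic model, subtracting, and taking a delta-method interval gives +5.9 points (-2.1 to +13.8). With covariates, the predictions are averaged over all patients. The mismatch is therefore in the output reported, not in the model.

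**5. Expected primary failures.** 85 × (0.05 + 0.10) = 12.75, and 95 × 0.15 = 14.25. With treatment plus one covariate, that is 12.75/2 to 14.25/2 = 6.4 to 7.1 failures per parameter. With treatment plus four covariates it is 12.75/5 to 14.25/5 = 2.6 to 2.9.

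**The case against.** The strongest reply is that the protocol never mentions an odds ratio, does not tie the logistic model to the margin, and does not use it to decide non-inferiority. In a 1:1 randomised trial such a model is supportive, and its reporting scale could be left to a statistical analysis plan that is not shown. A standardised risk difference comes from this very model, so the choice of logistic regression is not an error. Most of this stands. The odds ratio is inferred as the model's customary output. What the reply does not remove is that section 8.2 does state a way to judge results, P < 0.05, and that rule does not address the margin.

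A reader might also infer that 13 to 14 failures make the model unstable, or that only one covariate is allowable. The documents do not support either. The number of covariates is not given, so failures per parameter cannot be fixed. The 13 to 14 figure also covers the primary outcome only, as section 8.1 gives no rates for total success or complications. The low count is a reason for restraint, not evidence of a failed model.

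Finally, one may say that the unadjusted chi-squared and Fisher tests, judged at P < 0.05, have the same weakness and matter more. That is true, but it is a separate point. Correcting the primary test would leave the sentence on adjustment unchanged.

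**Conclusion.** The point holds as a modest improvement. As written, the adjusted analysis of the primary outcome does not speak to the -8-point margin, because an odds ratio judged against 1 can be non-significant whether non-inferiority is met or not. The size of the mismatch is a margin-equivalent odds ratio running from 0.59 to 0.35 as control success goes from 85% to 95%.

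This rests on two assumptions: that logistic regression is meant for the binary outcomes, and that it would be reported in its usual form.

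One might infer that the trial's conclusion hangs on an odds ratio, or that logistic regression is unusable here. Section 8.2 assigns the model no role in the non-inferiority decision, and step 4 shows that it can yield the right quantity. The margin, the sample size and the primary conclusion are unaffected. The point does not extend to the secondary binary outcomes, for which no margin is set.

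**What to change.** Add one sentence to section 8.2, for the primary outcome only. It should say that the adjusted analysis is supportive, and that it uses the logistic model with a small set of covariates chosen in advance. It should also say that the result is a standardised (marginal) risk difference with a two-sided 95% confidence interval, read against -8 points, and that any odds ratio is secondary output. The covariate list itself can sit in the statistical analysis plan.

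The cost is one extra post-estimation step in Stata, which section 8.2 already names. No change to the design, the margin or the sample size is needed.
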